### Compliance

The participants will be daily monitored for symptoms of post-COVID-19 syndrome and related to *Basti* therapy-related side effects. Telephonic follow up will be done during the 2th, 3th, and 4th visits throughout the study. The study coordinator will contact the participants to monitor symptoms and ensure compliance. Medication logs will be maintained for intervention drug consumption. The drug compliance will be assessed at each follow-up visit by the patients and counting the number of empty containers returned and assessing the quantity of medicines consumed by the patient. Also, drug compliance report form will be provided to the study patients and filled by the patients and submitted to the investigators during the follow-up visit.

### Trial intervention

An intervention will be decided on the basis of *Santarpanottha* symptoms or *Apatarpanottha* symptoms.

#### Intervention arm (Group 1)

The *Santarpanottha* group will be treated in three stages: *Pachan, Shodhan,* and *Rasayan* in a sequence as follows:
*Pachan*
* (*conversion of toxins in removable form)—Ayurveda formulation *Guggulutiktak Kashaya* 10–30 ml BD orally after meals with warm water and *Gomutra arak* (cow urine distillate) for 3 to 5 days will be given. *Guggulutiktak Kashaya* is a classical Ayurvedic decoction used to treat diseases arising from over nutrition.
*Shodhan* (removal of toxins)—Classical *Ayurveda Yog Basti* treatment includes 8 days of per rectal medications as per classical Ayurved methods, i.e., *Anuvasan Basti* and *Niruh Basti* will be administered on alternate days. Processed sesame oil will be used for *Anuvasan Basti* 60–100 ml per rectally after meal OD given for alternate 3 days, and *Triphala* decoction mixed with processed sesame oil and cow urine distillate will be used for classical *Niruh Basti*. The dose of *Niruha Basti* will vary between 400 and 850 ml empty stomach OD given for alternate 3 days. The last two *Basti* will be *Anuvasan* that is processed sesame oil after meal. One will be given either *Anuvasan* or *Niruha* on alternate days from the 1st to 6th day. In the last 2 days, i.e., the 7th and 8th day, *Anuvasan* will be given.
*Rasayan* (rejuvenation)—After completion of classical *Yog Basti* treatment, *Rasayana* treatment will be given for 21 days. *Brahma Rasayana* will be used as a *Rasayana* in the dose of 10–30 g OD orally on an empty stomach in the morning with warm water for 21 days.

The exact dose for each patient will be finalized on the basis of Ayurveda-based parameters like *Koshtha*, *Agni*, and *Basti Nirgaman*.

#### Intervention arm (Group 2)

The *Apatarpanottha* group will also be treated in three stages: *Pachan, Shodhan, and Rasay*an in sequence as follows:
***Pachan*** (conversion of toxins in removable form)—Ayurveda formulation Tablet Laghumalini *Vasant* 250–500 mg BD orally after meals with water for 3 to 5 days.
***Shodhan*** (removal of toxins)—*Yog Basti* treatment includes 8 days of per rectal medications as per classical Ayurved methods, i.e., *Anuvasan Basti* and *Niruh Basti* will be administered on alternate days. *Kshirbala oil* will be used for *Anuvasan Basti* 60–100 ml per rectal after meal OD for 5 days. Milk processed in *Brihat Panchmula herbs* will be used for *Niruha* per rectal in dose 400–850 ml on an empty stomach OD given for alternate 3 days. One will be given either *Anuvasan* or *Niruha* on alternate days from the 1st to 6th day. The last 2 days, i.e., the 7th and 8th day, *Anuvasan* will be given.
***Rasayan*** (rejuvenation)—After completion of classical *Yog Basti* treatment, *Rasayana* treatment will be given for 21 days. *Kalyanak Ghrit* will be used 15–30 ml OD orally on an empty stomach in the morning with warm water for 21 days.

The exact dose for each patient in both groups will be finalized on the basis of Ayurveda-based parameters like *Koshtha, Agni*, and *Basti Nirgaman* (evacuation).

### Clinical outcomes

#### Primary outcome

To evaluate the efficacy of Guggulutiktak Kashayam followed by *Yog Basti* (*Triphala Kwath Niruh Basti, Tiltail Anuvasan Basti*) followed by *Brahma Rasayana* on symptoms of *Santarpanottha* post-COVID-19 syndrome in the period of 35 days.To evaluate the efficacy of Laghumalini Vasant followed by *Yog Basti* (*Brihatpanchmulsidhha Kshirbasti, Kshirbala tail Anuvasan Basti*) followed by *Kalyanak Ghrit* on symptoms *Apatarpanottha* post-COVID-19 syndrome in the period of 35 days.

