**Methods and analysis:**

We designed a prospective, open-labeled proof of concept pragmatic study. The study duration is 18 months, and the intervention period are 35 days from the day of enrollment of the patients. The patients will be treated on the basis of Ayurvedic classification of *Santarpanottha* (over nutrition) symptoms and *Apatarpanottha (lack of nutrition)* symptoms. The *Santarpanottha* group will be treated within 3–5 days of oral *Guggulu Tiktak Kashayam* followed by 8 days of *Yog Basti* treatment and then 21 days of *Rasayana* therapy with *Brahma Rasayan*. The *Apatarpanottha* group will be treated within 3–5 days of oral *Laghumalini Vasant*, followed by 8 days of *Yog Basti* treatment and then 21 days of *Kalyanak Ghrit.*

The outcome measures of this study will be to evaluate the changes in fatigue severity scale, MMRC dyspnea chest pain scale, pain score assessed by VAS scale, smell and taste scale, WOMAC scale, Hamilton depression scale, Hamilton anxiety scale, Insomnia Severity Index, change in Cough Severity Index, facial aging scale, dizziness scale, Pittsburgh Sleep Severity Quality Index, functional status scale, and heart palpitation scale.

All adverse events will be monitored at each time throughout the study visit time. A total of 24 participants will be recruited to demonstrate with 95% confidence interval and 80% power.

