## Objectives

To evaluate the efficacy of Guggulutiktak Kashayam followed by *Yog Basti* (*Triphala Decoction Niruh Basti, medicated oil Anuvasan Basti*) followed by *Brahma Rasayana* on symptoms of *Santarpanottha* post-COVID-19 syndrome in the period of 35 days.To evaluate the efficacy of tablet Laghumalini Vasant followed by *Yog Basti* (*Brihatpanchmulsidhha Kshirbasti [medicated milk enema], Kshirbala tail [medicated oil* processed in milk*] Anuvasan Basti*) followed by *Kalyanak Ghrit* (medicated cow ghee) on symptoms *Apatarpanottha* post-COVID-19 syndrome in period of 35 days.

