## Methods and analysis

### Patient and public involvement

This study protocol is developed to evaluate the effect of *Basti* and *Rasayana* therapy to modulate immune responses in post-COVID-19 syndrome. Patients were not involved in the design, recruitment, or conduct of the study. The details of procedures with times are explained in Table 1.

**Table 1 Tab1:** Summary of activities

	Enrollment	Allocation	Post allocation			Completion
Timepoint	Screening Day 0	Day 1	Days 3 to 5	Days 5 to 13	Days 14 to 34	Day 35

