### Statistical analysis

#### Sample size and power

The sample size for the study is calculated by using the formula with assumption which is made after the pilot study on 4 patients. The assumption made is that our treatment will reduce total symptoms by at least 40% with 95% confidence interval (*α* = 0.05) and 80% power of the study and expecting a dropout rate of 20%. Hence, a total of 24 patients will be recruited.

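### The primary outcome section names no measured variable, and the total-symptoms quantity that sized the trial is undefined and is not listed as an outcome

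*Protocol article*

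**What the plan says.** Under Primary outcome the protocol article has two statements, one per treatment group. They begin "To evaluate the efficacy of Guggulutiktak Kashayam followed by" and "To evaluate the efficacy of Laghumalini Vasant followed by", and each goes on to name the regimen, the symptom type and a 35-day period. The Objectives section carries the same two statements with small differences of wording; its second begins "To evaluate the efficacy of tablet Laghumalini Vasant followed by".

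Secondary outcomes lists 15 instruments: fatigue, dyspnea, chest pain, VAS pain, smell and taste, WOMAC, Hamilton depression, Hamilton anxiety, insomnia, cough, facial aging, dizziness, Pittsburgh sleep, functional status and palpitation. The abstract gives the scales without any order: "The outcome measures of this study will be to evaluate the changes in fatigue severity scale", followed by the rest.

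Sample size and power assumes that "our treatment will reduce total symptoms by at least 40" per cent, with α = 0.05, 80% power and 20% dropout, giving 24 patients in total. The Analysis section lists tests by type of data and ties none of them to a primary variable.

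**The concern.** A primary outcome should be something that can be calculated from the case record form: an instrument or score, a time point and a summary. Here an objective stands where the variable should be, and every measured instrument has been placed on the secondary list, so none is left to be primary.

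Two things follow. First, the planning statement has no object: a 40% reduction with 80% power describes a quantity the trial does not list among its outcomes. Second, each group's sole objective is efficacy on symptoms, and no stated result would confirm or refute it. After the data are in, the conclusion could be drawn from any of the 15 scales in either group. The study is open-label and most scales are symptom ratings, which makes fixing the variable in advance more important.

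**Working it through.** **1. Can the primary variable be recovered from the text?**

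| Section | What it supplies | What it lacks |
|---|---|---|
| Primary outcome | domain (symptoms), period (35 days) | instrument, score, summary, success criterion |
| Secondary outcomes | 15 named scales | all labelled secondary |
| Sample size and power | total symptoms, reduction of at least 40% | definition, scoring, place in an outcome list |
| Inclusion criteria | entry on at least 4 symptoms, also given as a percentage, so a finite list is presupposed | the list itself |
| Table 1 | a signs and symptoms assessment at Day 0, Days 14–34 and Day 35, in a row separate from the clinical scales | items, scoring, total |

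A symptom total distinct from the 15 scales is the likely intention, but no section defines it or calls it an outcome.

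**2. The plan's own figure, N = 24.** It can be neither reproduced nor refuted, because no SD, formula or variable is given. Working backwards: 19/(1 − 0.20) = 23.75, rounded up to 24, or 20 × 1.2 = 24. Assume a paired comparison of all patients together, two-sided 5%, 80% power. Then the standardised effect d = (1.960 + 0.842)/√n is 0.643 at n = 19 and 0.626 at n = 20. For a 40-point mean reduction the SD of percent change would have to be 40/0.643 = 62 or 40/0.626 = 64 points. Nothing in the article allows that to be checked.

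**3. What the open choice could cost.** Inputs: 15 scales (Secondary outcomes); 2 groups with assignment by symptom type ("An intervention will be decided on the basis of" the symptom category, under Trial intervention) and a separate objective each; α = 0.05. Assumptions: every scale tested once, two-sided, with exact 5% size and no true change. Correlations of 0.3 and 0.5 are also assumed; the article gives none.

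A false efficacy claim needs significance in the direction of improvement, so the rate per test is 2.5%.

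- Independent, one group: 1 − 0.975^15 = 0.316.
- Independent, both groups: 1 − 0.975^30 = 0.532.
- Equal correlation ρ with common factor G: p(G) = 1 − Φ((1.96 − √ρ·G)/√(1 − ρ)), and the chance is 1 − E[(1 − p(G))^15]. This gives 0.235 at ρ = 0.3 and 0.181 at ρ = 0.5.
- Both groups (different patients, so independent): 1 − (1 − 0.235)² = 0.41 and 1 − (1 − 0.181)² = 0.33.

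| | independent | ρ = 0.3 | ρ = 0.5 |
|---|---|---|---|
| False improvement, one group | 32% | 23% | 18% |
| False improvement, both groups | 53% | 41% | 33% |
| Any significant change, one group | 54% | 46% | 36% |
| Any significant change, both groups | 79% | 70–71% | 59% |

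The last two rows use 5% per test (1 − 0.95^15 = 0.537 and 1 − 0.95^30 = 0.785 under independence).

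**4. With one named variable per group.** At two-sided 5%, the rate of any false positive is 5% per group and 1 − 0.95² = 9.75% over both. False improvement is 2.5% per group and 1 − 0.975² = 4.9% over both.

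**The case against.** The strongest reply is that the text is less empty than it looks. It fixes a domain and a time horizon, the sample size section points to a symptom total, and the scales are already labelled secondary. The abstract's unordered list may be mere condensation, this is a small unfunded proof-of-concept thesis study, and a multiplicity rule for secondary scales could sit in an analysis plan that is not shown.

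Much of that stands. A reader might infer that the protocol plans 30 tests at 5% and would report any significant one as efficacy. It does not say so: α appears only in the sample size text, with sidedness unstated and no rule for what counts as success. Nor is there a stated 5% error rate for the whole trial against which 79% could be set. Counting significant worsening as efficacy also overstates the risk, so the false-improvement rows are the relevant ones.

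Even those are probably upper bounds. The Wilcoxon signed-rank test planned for subjective criteria cannot reach an exact two-sided p below 2/2^5 = 0.0625 with five or fewer non-zero differences. With 24 patients, 20% dropout and entry on as few as four symptoms, some scales may have that few changes.

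What does not stand is leaving the primary variable itself to another document. The article has a section for it and fills that section with the objectives, while the quantity used for sizing is absent from both outcome lists.

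**Conclusion.** The point holds. The stated primary outcome cannot be calculated, every named scale is secondary, and the sizing quantity is undefined and unlisted. The 40% and 80% figures therefore describe no listed outcome, and the choice of what demonstrates efficacy is left open until after the data are seen.

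The exposure, if each of the 15 scales were used as a test, is roughly 18% to 32% per group and 33% to 53% over both for at least one false improvement. This rests on the assumed correlations (0 to 0.5) and on exact two-sided 5% tests. It measures what the wording permits and does not predict what the investigators will do. The finding depends on the missing primary variable, not on the lack of a multiplicity rule.

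A reader might also infer that 24 patients is the wrong number. The article does not support that; the figure is uncheckable as reported.

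**What to change.** Replace the text under Primary outcome with one variable: the change in a defined total symptom score from Day 0 to Day 35. Build it from the symptom list used for eligibility and the signs and symptoms assessment already scheduled in Table 1, with the items and scoring fixed before any data are analysed. Analyse it once in each group, report the estimate with its 95% CI, and set the percent reduction beside the planned 40%. Use the same name in the abstract and in the sample size section.

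Keep the 15 scales as secondary and supportive, reported as estimates with CIs, with no efficacy claim resting on a single p-value.

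The cost is modest but goes beyond rewording. Table 1 schedules an assessment and does not describe a scored checklist, so the items and scoring must be written down. If they were not recorded uniformly, the case record form may need attention. No extra visit is required. The investigators also give up the option of letting one significant scale carry the conclusion.

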#### Secondary outcomes

Change in fatigue score assessed by fatigue severity scaledyspnea score assessed by MMRC dyspnea scalechest pain assessed by chest pain scalepain score assessed by VAS scaleChange in score assessed by smell and taste scaleChange in score assessed by WOMAC scaleDepression score assessed by Hamilton depression scaleAnxiety score assessed by Hamilton anxiety scaleChange in score assessed by Insomnia Severity IndexChange in Cough Severity IndexChange in score facial aging scaleChange in score assessed by dizziness scaleChange in sleep quality assessed by Pittsburgh Severity Quality IndexChange in the quality of life assessed by functional status scaleChange in score assessed by heart palpitation scale

### Adverse events

All adverse events (AEs) during the therapy will be recorded and monitored as per ICH-GCP (2016) [15] and ICMR guidelines [16]. The safety of the participants would also be assessed in case of all withdrawals. All adverse events will be recorded and followed till resolution. All adverse events will be classified by the study physician and recorded in the AE form. The Data Safety Monitoring Board (DSMB) will be formed to monitor the safety of the participants and assess the safety data. Clinical assessments will be carried out as per Table 1.

### Concomitant medication

For the patients registered under the trial study, investigators will be instructed to avoid the use of other drugs on their own view and consult the investigators for any illness, symptom, and complaint or if they feel anything unusual. The investigator will record any medication(s) he/she may have prescribed for this any emergency medical condition, and the use of any concomitant medication will be prescribed only by the investigator mentioned in its case record form.

### Statistical analysis

#### Sample size and power

The sample size for the study is calculated by using the formula with assumption which is made after the pilot study on 4 patients. The assumption made is that our treatment will reduce total symptoms by at least 40% with 95% confidence interval (*α* = 0.05) and 80% power of the study and expecting a dropout rate of 20%. Hence, a total of 24 patients will be recruited.

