The gastro-intestinal tract is the largest immunological organ in the body, and its resident microbiota are known to modulate host responses. In post-COVID-19 syndrome, gut microbiota composition is disturbed and it is also associated with disease severity and plasma concentrations of several cytokines and inflammatory markers. The patients with COVID-19 report persistent symptoms after recovery and subsequently develop dysbiotic gut microbiota. There are various immune-related health problems post-COVID-19 [3].

COVID-19 is correlated with *Abhishangaj Jvara (fever* arising due external cause*)* in *Ayurveda* [4]*.* Some patients who suffered from COVID-19 followed *Langhana* (fasting) while some have not followed [5]. Therefore, currently observed signs and symptoms of post-COVID-19 syndrome can be categorized into two groups, i.e., *Santarpanottha* (excessive nutrition) and *Apatarpanottha* (poor nutrition) symptoms as per correlations with *Astang Hrdayam Sutrasthan* 14 [6]. COVID-19 epidemic can be termed as “*Janapadodhvans Vyadi* (epidemic)”*.* Charka described this concept of epidemic, which have a causing factor like polluted *Vayu* (air)*, Jala* (water)*, Desh* (country), and *Kaal* (time). *Panchakarma* (five cleansing process) and *Rasayana* (rejuvenation) therapy are two important treatments that are advised by Charka for various *Janapadodhvans Vyadi* [7, 8].

It is evident that COVID-19 leads to debilitation, and condition is more likely *Apatarpanothha*.

Recent articles have shown that post-COVID metabolic dysfunction can lead to insulin résistance and obesity. Recent researches have that there are metabolic clues that can lead to bidirectional pathologies.

Obesity, insulin resistance, development of obese type 2 DM may fall under *Santarpanottha*.

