#### Analysis

Results and observation seen in the research will be analyzed by proper statistical methods. The data collected in the CRF will be computerized in an Excel file for a separate group. Wilcoxon signed-rank test, Mann–Whitney, chi-square, and non-parametric ANOVA will be carried out to evaluate the effect on subjective criteria. Paired *t* test, unpaired *t* test, and ANOVA will be carried for normally distributed parametric/objective criteria**.**

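### The 80% power is stated once for an unallocated total of 24, so it is neither shown nor secured for either of the two group-specific primary objectives

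*Protocol article*

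**What the plan says.** *Sample size and power* assumes that "our treatment will reduce total symptoms by at least 40" per cent, "with 95% confidence interval (*α* = 0.05) and 80% power of the study", with 20% dropout, after a pilot in 4 patients. It concludes: "Hence, a total of 24 patients will be recruited". The abstract repeats the claim: "A total of 24 participants will be recruited to demonstrate with 95% confidence interval and 80% power". *Recruitment, screening, and consent* likewise gives only the overall 24 as the point where enrolment ends.

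*Objectives* and *Primary outcome* list two efficacy aims. One is for the Santarpanottha group. The other, for the Apatarpanottha group, begins "To evaluate the efficacy of Laghumalini Vasant followed by" and names a different sequence of treatments. *Trial intervention* assigns the regimen by symptom type. No ratio, quota or minimum per group appears in the text shown.

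*Analysis* states: "The data collected in the CRF will be computerized in an Excel file for a separate group". It lists within-group tests (signed-rank, paired t) and between-group tests, and ties none of them to the primary outcome.

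**The concern.** The power statement and the objectives describe different things. Power is claimed once, for the study and for a single treatment. The aims are two, each answered in a subset of the 24 by a different regimen. Because patients arrive in a group by clinical type, the size of each subset is left to chance.

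The *Introduction* suggests that balance should not be taken for granted: "It is evident that COVID-19 leads to debilitation, and condition is more likely" to be of the Apatarpanottha type.

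The stake is interpretation. A null result in a group of 5 to 10 patients could be read as evidence of no effect from a study advertised as having 80% power. In a very small group, one of the listed tests could not reach significance whatever the data.

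**Working it through.** **Inputs.** From *Sample size and power*: α = 0.05, power 80%, 40% reduction in total symptoms, dropout 20%, total 24. Assumed here because the article does not state them: two-sided testing, and a paired (one-sample) t test on the change. Write d for mean change divided by the SD of the change.

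**1. The plan's own figure.** Only the dropout step can be checked. 24 × 0.8 = 19.2, so about 19 evaluable; in reverse, 19 / 0.8 = 23.75, rounded up to 24. The power step cannot be reproduced uniquely, because quite different routes lead to 24:
- pooled: about 19 evaluable, inflated for dropout to 24;
- two groups: 10 evaluable × 1.2 = 12 each, 24 in total;
- a precision formula for a proportion of 0.4 with margin 0.2: 1.96² × 0.4 × 0.6 / 0.2² = 23.05, rounded up to 24, with no power or dropout term.

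**2. Power formula.** Power = P(T > t with n − 1 df at 0.975), where T is noncentral t with n − 1 df and noncentrality d√n.

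**3. Pooled reading.** Setting power to 0.80 at n = 19 gives d = 0.68. The normal approximation gives (1.96 + 0.84)/√19 = 0.64. For a 40-point mean reduction, d = 0.68 corresponds to an SD of change of 40/0.68 = 59 points. An even split of 19 is 9 and 10.

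**4. Twelve-per-group reading.** Setting power to 0.80 at n = 10 gives d = 0.996, an SD of change of about 40 points. With 20% dropout, 12 × 0.8 = 9.6, so 9 or 10 are evaluable.

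| Evaluable in the group | Power at d = 0.68 (pooled reading) | Power at d = 0.996 (12 per group) |
|---|---|---|
| 6 | 27% | 50% |
| 9 | 43% | 74% |
| 10 | 48% | 80% |
| 14 | 65% | 93% |

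On the pooled reading, even 18 of the 19 in one group gives that group only 78%. Starting from 20 evaluable instead of 19 (d = 0.66) changes little: 46% at 10, and 63% and 26% for a 14/6 split.

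**5. Signed-rank floor.** The smallest exact two-sided p is 2/2ⁿ. For n = 5 this is 0.0625, above 0.05; for n = 6 it is 0.031.

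**6. What 9–10 evaluable patients can support.** 80% power needs d = 0.996 (n = 10) or 1.067 (n = 9). The 95% CI half-width, in SDs of the change, is t/√n: 2.262/√10 = 0.72 and 2.306/√9 = 0.77.

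**The case against.** The article never says that 24 was computed for a pooled test. Twelve per group, with 10 evaluable in each, fits the total as well, and an even split would then meet 80% in both groups. Put in terms of the SD, 10 evaluable patients suffice for a 40-point reduction if the SD of the change is about 40 points or less. No arithmetic in the section is shown to be false. The SD, formula and per-group number may be in the full protocol, and the flow chart and supplement are not visible here. The study is an unfunded, open-label proof of concept, for which a small sample is legitimate, and estimates with confidence intervals would still be informative.

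Much of this stands. A reader might infer that neither group can have 80% power; that follows only on the pooled reading. A reader might also multiply the two group powers, but the protocol does not require both objectives to succeed. Nor do the documents support a particular imbalance: the *Introduction* goes on to describe a metabolic route to the other symptom type and gives no proportion. The signed-rank floor applies only if a group ends with 5 or fewer evaluable patients and the exact two-sided test is used; paired t tests are listed too. Separate testing is itself inferred from the objectives and the per-group data files.

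What remains is not an omission that can be left to a fuller document. The article publishes a power figure, in the abstract as well, that is attached to neither of its stated objectives. Even on the favourable reading, nothing in the text shown produces the 10/10 evaluable split it needs.

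**Conclusion.** The point holds in this form: the stated 80% power is not shown or secured for either primary objective. On the pooled reading, which the wording about the power of the study and a total of 24 most naturally suggests, an even split leaves each group well below 80%, and no realistic split rescues either. On the 12-per-group reading, 80% is met only if each group keeps 10 evaluable patients; an uneven split takes the smaller group below it. The percentages rest on an assumed two-sided paired t test and on standardised effects back-calculated from the 80% claim, not on an SD from the documents. How likely a group is to become too small for the signed-rank test cannot be stated without assuming a share for each type.

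**What to change.** Keep the total of 24 and cap each group at 12. In *Sample size and power* and in the abstract, replace the single power claim with a per-group statement along these lines: *with 9–10 evaluable patients per group, a two-sided paired t test at 0.05 has 80% power only for a standardised change of about 1.0–1.07 or larger; the expected 95% CI half-width is about 0.72–0.77 SD of the change.* State also whether 24 was derived for the pooled sample or as 12 per group.

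The cost is wording in two places, possibly slower recruitment of the rarer type (and some eligible patients of the commoner type turned away), and a less favourable published figure. No extra patients are needed. The cap prevents a very lopsided split but does not restore 80% power at the pooled effect. That would need 19–20 evaluable per group: 19/0.8 = 23.75, rounded up to 24, or 20/0.8 = 25 recruited per group, so 48–50 in total. For a proof of concept, the restated claim is the proportionate choice.
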